### Sample size and justification

128 participants are required in order to have 80% power to detect a difference in mean change of the primary outcome measure. This assumes equal standard deviations of 16 points and using a pre-specified significance level of *p *< 0.05. Assuming 20% attrition rates, it is proposed to recruit 158 participants to the study (79 intervention arm, 79 control arm).

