### Statistical analysis

SPSS V.18 will be used for the analysis of the results. The two groups will be described in terms of their baseline characteristics. Our primary outcome will be the CDI post intervention. A regression model will be used to compare the two groups in terms of the CDI score post intervention conditional on baseline score. No other confounders will be adjusted for unless there appears to be an imbalance at baseline between the two groups on pre-specified covariates that are considered to influence outcome. For secondary outcomes, similar models will be built all conditional on the relevant baseline score in addition to baseline CDI score. Analyses will be intention-to-treat and conducted on a dataset where codes for the two intervention groups are unlabeled. All estimates of effect sizes and numbers needed to treat will be reported with 95% confidence intervals. One of the potential problems with early studies testing a relatively new intervention with a group in whom it is largely untested is that the results may be skewed in a positive direction. To minimise this potential effect, the statistical analyses will be conducted independently of the research team. Qualitative analysis of the focus groups and interviews will be conducted using NVivo 9 in order to code the information and look for relevant trends and themes within the data.

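### Minor arithmetic error: 128 evaluable participants at 20% attrition needs 160 recruits; the stated 158 leaves about 126

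*Protocol article*

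**What the plan says.** The protocol article, under Sample size and justification, gives the requirement as follows: "128 participants are required in order to have 80% power to detect a difference in mean change of the primary outcome measure". The inputs are an SD of 16 ("This assumes equal standard deviations of 16 points") and a 5% significance level. The section then allows for loss and sets the recruitment target: "Assuming 20% attrition rates, it is proposed to recruit 158 participants to the study (79 intervention arm, 79 control arm". The Abstract repeats the figure of 158.

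Under Statistical analysis, the primary comparison is described differently from the mean change named in the sample-size section: "A regression model will be used to compare the two groups in terms of the CDI score post intervention conditional on baseline score".

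**The concern.** The section links three numbers: the size required (128), the loss expected (20%) and the number to recruit (158). Any two of them fix the third, and here the third does not follow. On its own assumption, the plan ends with fewer evaluable participants than it says it needs.

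What is at stake is the accuracy of a headline design figure. A reader takes the paragraph to say that 80% power is retained after 20% loss, and as written that is not quite so. Stopping rules and discontinuation also names failure to recruit the required sample as a ground for stopping, which is a further reason for the required and recruited numbers to agree. The practical consequence has to be sized before any weight is put on it.

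**Working it through.** **Inputs from the protocol article (Sample size and justification):** 128 required; 80% power; SD 16 in each arm; significance level 0.05; attrition 20%; 158 recruited as 79 + 79.

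**Assumed, because the article does not state them:** a two-sided test, and a target difference of 8 points (0.5 SD).

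**Step 1. Attrition arithmetic (no assumptions needed).**
- Recruits needed = required/(1 − attrition) = 128/(1 − 0.20) = 160, or 64/0.8 = 80 per arm. Stated: 158, or 79 per arm.
- Evaluable at the stated target = 158 × 0.80 = 126.4, or 79 × 0.80 = 63.2 per arm.
- Attrition at which 158 leaves exactly 128 = 1 − 128/158 = 0.190, that is 19.0%.
- Multiplying by 1.2, a common slip, gives 128 × 1.2 = 153.6, so 154. That does not explain 158 either.

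**Step 2. Reproducing the plan's figures.** With 64 per arm, SD 16, 80% power and two-sided 5%, the implied difference is 16 × √(2/64) × (1.960 + 0.842) = 7.92 points by the normal approximation, or 7.99 by the t-test. Eight points (d = 0.5) is therefore a natural reading. With that difference:
- the t-test needs 63.8, so 64 per arm, which gives 128;
- the normal approximation needs 63 per arm, and 63/0.8 = 78.75, so 79 per arm, which gives 158.

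Each figure can be reproduced, but by a different method. A mixture of the two calculations is a plausible source of the mismatch. It is an inference, since it rests on the assumed 8 points.

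**Step 3. Cost in power (8 points, SD 16, two-sided 5%, unadjusted).**

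| Per arm | t-test | Normal approximation |
|---|---|---|
| 64 | 80.1% | 80.7% |
| 63 | 79.5% | 80.1% |

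The loss is about 0.6 percentage points on either method.

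**Step 4. Side check on the planned analysis.** Let r be the correlation between baseline and post-intervention score, with equal variance at the two times. Adjusting for baseline gives a residual SD of
- 16 × √(1 − r²) if 16 is the raw-score SD;
- 16 × √((1 + r)/2) if 16 is the SD of change.

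Neither can exceed 16. Power of the adjusted comparison for 8 points with 63 per arm, at assumed values of r:

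| r | 16 = raw-score SD | 16 = SD of change |
|---|---|---|
| 0.2 | 81% | 95% |
| 0.3 | 83% | 93% |
| 0.5 | 90% | 90% |
| 0.7 | 97% | 86% |

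Every entry is above 80%.

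**The case against.** The strongest reply is that this is rounding. The gap is 2 in 160 (1.3%), attrition is a forecast that nobody expects to hold to the percentage point, and a loss of 19% instead of 20% closes it. 158 also follows exactly from 63 per arm, so the target may be right for the calculation behind it. All of this limits the weight of the point. It does not make the sentence correct: 128/0.8 is exactly 160, with nothing to round, and 158 lies below it.

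A reader might go further and infer that the trial is underpowered, because power is stated for mean change while the regression compares post-intervention scores conditional on baseline. The documents do not support that. Power for a change score could fall well short of 80% only if 16 were the raw-score SD and the baseline-to-post correlation were low, and the article does not plan a change-score analysis. For the analysis it does plan, the residual SD is at most 16 under either reading, so the stated 80% errs on the safe side.

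A reader might also want to make the missing target difference, the undefined SD and the missing correlation into the finding. They do prevent a full check of 128. But this is a journal article that condenses a fuller protocol not shown here, and such detail may stand there.

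**Conclusion.** The sample-size paragraph contains a minor arithmetic error. At 20% attrition, 128 evaluable participants require 160 recruits; 158 recruits leave about 126, or 63 per arm. This rests only on figures in the article.

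The shortfall is two recruits. Its effect on power, 79.5% against 80.1%, holds for an unadjusted two-sided t-test and an assumed 8-point difference. No design decision turns on it.

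The difference in wording between mean change and the baseline-adjusted score is a side remark. With the same assumed difference and 63 per arm, the planned analysis has 81% to 97% power for correlations between 0.2 and 0.7, whichever way the SD of 16 is read. That range also assumes equal variance at baseline and post-intervention.

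**What to change.** Correct the sentence and leave recruitment at 158. Either of these will do:

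- Keep 20% attrition and state that 158 recruits give about 126 evaluable participants (63 per arm), with the power statement matched to that number. If the intended difference is 8 points, the unadjusted t-test figure is 79.5%.
- Keep 128 evaluable and state that this corresponds to 19% attrition.

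The first is cleaner because it leaves the attrition assumption alone. In the same edit, one clause could say that power was calculated for a simpler comparison than the baseline-adjusted model and is conservative for it.

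The cost is a sentence or two. One stated figure becomes very slightly less favourable. No more participants are needed, and the 158 in the Abstract can stand.

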### Stopping rules and discontinuation

The Trial will be stopped if there are significant adverse events that cannot be remedied, if there is a significant failure to recruit the required sample and if requested by the funder or sponsor.

### Randomisation and blinding

Allocated to experimental or control arm will be by computer generated numbers by a researcher not associated with the study. Measurements of baseline, outcome and follow-up measures will be taken by a researcher not associated with the study. Baseline outcome measures will be taken after random allocation. The exercise therapist and focus group facilitator will only know which participants get the exercise intervention.

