### Procedure

The intervention group will undertake 12 × 60 minute aerobic exercise sessions, in groups of 5-10, tailored to participants' exercise levels and preferences led by a qualified exercise therapist. The intervention group will also receive psychosocial and motivational support throughout each session to facilitate ongoing participation and enduring change. The motivational coaching will consist of behaviour modification: goal setting, self-monitoring, social support, enhancing self-efficacy and shaping.

Participants will have baseline measures taken at the initial session. Outcome measures will be repeated at post intervention in the final session and at 6 month follow up at a location that suits the participant.

Participants in the intervention group will be invited to participate in focus groups and face-to-face interviews following completion of the exercise programme. These will take place at a location agreed with participants and researchers. It is hoped that these will be conducted at the centres at which the exercise takes place. The data will be recorded on an audio tape with the informed consent from the participants and their legal guardians. The facilitator will also take written notes which will help identify the participants in the recording. Data will be transcribed, coded and analysed for patterns, themes and sub-categories, paying particular attention to outliers and rival explanations given by participants.

The control group will receive usual care throughout the 12 week intervention period. Outcome measures will be taken within the same week as the paired intervention group; at baseline, post intervention (12 weeks later) and at 6 month follow up.

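### Baseline CDI-2 is taken after allocation, at the first session for the exercise arm, yet it is the covariate in the primary and all secondary models, so allocation can influence the adjustment

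*Protocol article*

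**What the plan says.** The order of events is stated outright. Under Randomisation and blinding, the article says: "Baseline outcome measures will be taken after random allocation". The Procedure section gives the occasion: "Participants will have baseline measures taken at the initial session". Control-arm measurement is tied to the start of the matching exercise group: "Outcome measures will be taken within the same week as the paired intervention group; at baseline, post intervention (12 weeks later) and at 6 month" follow-up. No section places a baseline before allocation or says that participants are unaware of their arm.

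Under Statistical analysis, the primary model will "compare the two groups in terms of the CDI score post intervention conditional on baseline score". For the secondary outcomes, "similar models will be built all conditional on the relevant baseline score in addition to baseline CDI score". The population is also fixed: "Analyses will be intention-to-treat".

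Two safeguards are described. One is independent assessment: "Measurements of baseline, outcome and follow-up measures will be taken by a researcher not associated with the study". The other is an analysis dataset with unlabelled group codes.

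A CDI before randomisation appears only in the Screening section, for referrals from community or voluntary services outside mental health. It is not named as the baseline for the model.

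**The concern.** Adjusting for baseline in a randomised trial is safe because a score taken before allocation cannot depend on allocation. Any baseline difference between the arms is then chance, and the regression removes it. Once the score is taken after allocation, part of the difference may be a consequence of allocation, and the regression removes that part too.

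The conditions for this are present here. The score is a self-report of mood. No participant blinding is described, and someone attending a first exercise session knows which arm they are in. Independent assessors and masked codes guard against assessor and analyst bias; they do not protect the participant's own answers.

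The primary estimate and every secondary estimate depend on this covariate. A larger sample would not remove the bias, and no later analysis plan can recover a pre-allocation score that was never collected.

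The second concern is missing data. In the exercise arm the baseline depends on attending, whereas controls have no session to miss. The article's abstract itself notes that compliance with prescribed exercise is generally low. Some allocated participants may therefore have no baseline, and their share may differ between arms.

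**Working it through.** **1. Reference difference.** The sample size section gives 128 evaluable participants, SD 16, 80% power and p < 0.05, but no target difference. Taking 64 per arm and a two-sided 5% test (sidedness is not stated):

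difference = 16 × (1.960 + 0.842) × √(2/64) = 7.9 points (normal approximation); the t-test version gives 8.0.

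Working forwards from 8 points, the t-test needs 64 per arm, or 128. The recruitment figure also reproduces within rounding: 128/0.8 = 160. The normal-approximation total of 126 gives 126/0.8 = 157.5, which rounds up to the stated 158. So about 8 points is a fair reading of what the trial is sized for.

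**2. Bias.** Let d be the baseline difference caused by allocation (exercise minus control) and b the within-arm slope of post-intervention CDI on measured baseline.

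adjusted effect = post-intervention difference − b × baseline difference

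The expected bias is therefore −b × d. A lower CDI score is better, so a negative treatment effect favours exercise.

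**3. Illustration.** The article gives neither b nor d. Assuming b = 0.3 to 0.7 and a 2-point shift:

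| Slope b | Bias if d = −2 | Bias if d = +2 | Share of 8 points |
|---|---|---|---|
| 0.3 | +0.6 | −0.6 | 7.5% |
| 0.5 | +1.0 | −1.0 | 12.5% |
| 0.7 | +1.4 | −1.4 | 17.5% |

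A lower exercise-arm baseline (d = −2) makes exercise look worse than it is. A higher one (d = +2) makes it look better.

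**4. Simulation.** With 64 per arm, SD 16 and 3,000 runs per setting, the estimated bias for d = −2 was 0.6, 1.1 and 1.4 points at slopes 0.3, 0.5 and 0.7, matching the formula.

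- With no true effect, the rejection rate was 5.6%, 7.9% and 10.2%, against 4.4%, 5.3% and 5.1% without a shift. Simulation error is about √(0.05 × 0.95/3000) = 0.4 percentage points, so the lowest-slope figure is barely distinguishable from 5%.
- With a true 8-point benefit, power fell from 84% to 77%, from 89% to 80%, and from 98% to 90%.

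**5. Missing baselines.** Suppose 5% to 20% of the 79 exercise participants (4 to 16 people) never attend and are lost to the analysis, on top of 20% attrition. Power for 8 points then falls from about 80% to between 79% and 75%. The loss of power is modest. The larger issue is that those missing would come from one arm only and would be selected by attendance.

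**The case against.** Several stronger readings are tempting, and the article does not support them.

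- **That the bias flatters exercise.** A reader might infer a false-positive risk, since the article itself worries about results skewed in a positive direction. The most obvious mechanisms, hopeful exercise participants and disappointed controls, both lower the exercise baseline relative to control. That biases against exercise. The opposite direction is possible but cannot be assumed.
- **That the CDI score triggers extra adjustment.** The article adjusts for other confounders only "unless there appears to be an imbalance at baseline between the two groups on pre-specified covariates". These are covariates other than the baseline score and are not listed, so nothing shows that allocation could change them.
- **That the planned model drops non-starters.** The article is silent on missing baselines, which are commonly handled in the analysis plan. Nor does it say that a non-attender would go unmeasured. Only the risk follows from the text.
- **That the first session contaminates the score.** Motivational support runs through each session, but the article does not say whether the questionnaire comes before or after it begins. When controls learn their allocation is not stated either.
- **That the bias is a larger share of a smaller target.** This would need a smaller SD, and the only SD in the article is 16.

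There is also a practical case for the present timing. Sessions run in groups of 5 to 10, and same-week measurement keeps both arms aligned with the 12-week period. A pre-allocation baseline may mean another contact while a group fills. This is a fair cost, but alignment does not require allocation to come first.

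What remains after these limits is a stated sequence, rather than a detail left to another document, which exposes the main covariate to allocation.

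**Conclusion.** The point holds in a limited form. The article fixes a post-allocation baseline and uses it as the covariate in the primary and all secondary models, so the adjusted effects can be biased by minus slope times the allocation-induced baseline difference. Neither the size nor the direction can be determined from the article. The illustrative 0.6 to 1.4 points, about 8% to 18% of an 8-point difference, rests on an assumed slope of 0.3 to 0.7, an assumed 2-point shift, the stated SD of 16 and a two-sided test. A different SD would change the percentages but not the points. Missing baselines among exercise-arm non-starters are a plausible secondary problem that could differ by arm and would strain the intention-to-treat claim, but the article does not say that these participants would be excluded.

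**What to change.** Amend Randomisation and blinding and Procedure so that they agree on one sequence: consent; then all baseline measures, taken by the same independent assessor; then allocation made or disclosed; then the start of the group, with a fixed short window between baseline and start. In Statistical analysis, name that pre-allocation score as the baseline covariate for everyone randomised, in the primary and secondary models.

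The instruments, assessor and sample size (128 evaluable, 158 recruited) stay the same. Baseline can be taken as each batch of participants assembles, which keeps control measurement paired with the exercise group. The cost is a short amendment, a somewhat older baseline when the group starts, and possibly one separate contact per participant.

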### Statistical analysis

SPSS V.18 will be used for the analysis of the results. The two groups will be described in terms of their baseline characteristics. Our primary outcome will be the CDI post intervention. A regression model will be used to compare the two groups in terms of the CDI score post intervention conditional on baseline score. No other confounders will be adjusted for unless there appears to be an imbalance at baseline between the two groups on pre-specified covariates that are considered to influence outcome. For secondary outcomes, similar models will be built all conditional on the relevant baseline score in addition to baseline CDI score. Analyses will be intention-to-treat and conducted on a dataset where codes for the two intervention groups are unlabeled. All estimates of effect sizes and numbers needed to treat will be reported with 95% confidence intervals. One of the potential problems with early studies testing a relatively new intervention with a group in whom it is largely untested is that the results may be skewed in a positive direction. To minimise this potential effect, the statistical analyses will be conducted independently of the research team. Qualitative analysis of the focus groups and interviews will be conducted using NVivo 9 in order to code the information and look for relevant trends and themes within the data.

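### Covariates other than baseline CDI enter the primary model only if baseline looks imbalanced, which makes the model data-dependent and gives up some precision

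*Protocol article*

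**What the plan says.** The Statistical analysis section of the protocol article defines the primary comparison as follows: "A regression model will be used to compare the two groups in terms of the CDI score post intervention conditional on baseline score". Baseline CDI is therefore in the model in every case.

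For anything further it states: "No other confounders will be adjusted for unless there appears to be an imbalance at baseline between the two groups on pre-specified covariates". It describes the candidates as "pre-specified covariates that are considered to influence outcome". The article gives neither the list nor a criterion for imbalance.

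The same section has two safeguards. The analysis is "conducted on a dataset where codes for the two intervention groups are unlabeled", and "the statistical analyses will be conducted independently of the research team".

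On size, the Sample size and justification section says "128 participants are required in order to have 80% power to detect a difference in mean change of the primary outcome measure", with "equal standard deviations of 16 points".

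**The concern.** Under randomisation, any baseline difference between the arms is chance. What adjustment gains depends on how strongly a covariate predicts the outcome, not on how far apart the arms happen to fall. The plan picks its candidates on the right property (prognosis) and then decides whether to use them on the wrong one (observed imbalance).

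Two things follow:

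- The primary model is not settled until baseline data have been compared by arm, so the primary estimate can come from one of several models.
- When a prognostic covariate looks balanced, which is the usual case, it is left out and its variance stays in the residual. The trial is sized for only 80% power, so even a few points have some value.

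**Working it through.** **Inputs from the article.** 128 analysable participants (64 per arm), SD 16, 80% power, significance level 0.05, baseline CDI always in the model.

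**Assumed inputs.** Two-sided test; target difference; number of covariates K and their independence; imbalance criterion; extra R² explained beyond baseline CDI.

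**1. The plan's own figure.** The article states no target difference, so 128 cannot be derived from its inputs alone. Solving backwards: (1.960 + 0.842) × 16 × √(2/64) = 7.92 points, or about 0.5 SD. With a difference of 8, the normal formula gives 63 per arm (126) and the t-based formula gives 64 per arm (128). I therefore use 8 points and treat 16 as the residual SD given baseline CDI.

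**2. How often chance triggers adjustment.** With criterion p<0.05, the chance of at least one flag is 1 − 0.95^K: 5% (K=1), 10% (K=2), 19% (K=4). With an absolute standardised difference above 0.2, each covariate is flagged with probability 2 × [1 − Φ(0.2/√(2/64))] = 0.258. The chance of at least one flag is then 26%, 45% and 70%. The model thus depends on the data, and how much depends on the criterion.

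**3. What fixed adjustment is worth, by formula.** SE = 16 × √(1 − R²) × √(2/64); power = Φ(8/SE − 1.96).

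| Extra R² | SE | Power | N for 80% power |
|---|---|---|---|
| 0 | 2.83 | 80.7% | 126 |
| 0.05 | 2.76 | 82.7% | 120 |
| 0.10 | 2.68 | 84.6% | 114 |
| 0.20 | 2.53 | 88.5% | 102 |
| 0.30 | 2.37 | 92.2% | 88 |

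**4. The rule against fixed adjustment, by simulation.** 64 per arm, K=4, p<0.05 trigger, baseline CDI in every model. The rule adds only the flagged covariates; fixed adjustment adds all four.

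| Extra R² | Power, rule | Power, fixed | Loss (points) |
|---|---|---|---|
| 0.05 | 79.5% | 80.9% | 1.4 |
| 0.10 | 80.0% | 82.6% | 2.6 |
| 0.25 | 81.4% | 89.1% | 7.7 |
| 0.49 | 81.4% | 96.9% | 15.5 |

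A second set of 8,000 runs per row gave losses of 0.9, 3.0, 7.9 and 15.7 points. At R² 0.05 and 0.10 the simulated loss is smaller than the formula's gain (82.7 − 80.7 = 2.0 and 84.6 − 80.7 = 3.9), because the rule sometimes adjusts and the fixed model spends degrees of freedom.

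The two larger rows correspond to four covariates each correlated 0.25 or 0.35 with the outcome beyond baseline CDI: 4 × 0.25² = 0.25 and 4 × 0.35² = 0.49.

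**5. Type I error.** Under the rule with the p<0.05 trigger it is about 3.5–4.8%. With the 0.2 standardised-difference trigger it falls as low as 3.0% (R² 0.30). The reason is that the baseline-only SE averages over all randomisations, including the imbalanced ones. The rule adjusts in just those, and keeps the same SE for the balanced ones, where it is too large.

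**6. Does the choice of model change the conclusion?** With a true difference of 8, R² of 0.1–0.3 and either trigger, the rule and the baseline-only model disagreed on significance in 1.4–9.7% of simulated trials.

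**The case against.** - **The list and threshold may be in the SAP.** This stands as far as it goes. An article commonly leaves such detail out, and its absence is not the point here. With a stated threshold, the rule would yield one determinate estimate. It would still select covariates on chance imbalance and still drop prognostic ones that look balanced.
- **The strongest covariate is already fixed.** This stands. Baseline CDI is always in the model, so much of the available precision is probably secured. If 0.5 SD refers to the raw outcome SD and the baseline–outcome correlation is 0.5–0.7 (assumed), baseline adjustment alone gives about 90–98% power, and an extra R² of 0.10 adds only about 1–3 points.
- **Masked codes and independent analysts protect the result.** They limit the scope for choosing a model by its result. They do not fix the model, since imbalance is visible between two unlabelled groups.
- **Inflated type I error might be inferred.** The stated rule does not produce it. Error rises to about 6.4–7.5% only if the analyst takes the better of the baseline-only and fully adjusted results, which the article does not propose and its safeguards work against.
- **The timing of baseline might be brought in**, since "Baseline outcome measures will be taken after random allocation". That sentence concerns outcome measures. Allocation cannot alter age or referral source, and the measure most exposed, baseline CDI, is in the model with or without the change proposed here. It is a separate issue and does not support this point.

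**Conclusion.** The point holds in a limited form. The article states a rule, not a gap: covariates that it regards as prognostic are used only when chance has made them look imbalanced. This leaves the primary model data-dependent (about 19% of trials triggered with four independent covariates at p<0.05, about 70% with a 0.2 standardised-difference criterion) and gives up precision.

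The size is uncertain because the extra R² is not in the document. For an effect of 0.5 SD on the residual scale and 64 per arm, the power loss is about 1 point at R² 0.05, 2–3 at 0.10 and about 8 at 0.25. A loss of 15 points or more might be inferred from the last row of the simulation, but it needs covariates that explain 49% of the variance left after baseline CDI. That is an extreme case, and nothing in the article supports it.

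The harm is an unfixed primary model and a modest loss of power. It is not a false-positive problem: applied mechanically, the rule is slightly conservative.

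**What to change.** Replace the conditional sentence with: *The primary model adjusts for baseline CDI-2 and a short list of pre-specified prognostic covariates in all cases, whatever the observed balance.*

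Choose the list before any data are seen by arm, from characteristics known at entry that allocation cannot alter. Age, referral source and treatment for depression at entry are examples that appear in the eligibility, recruitment or screening text. Sex could be added if it is recorded; the article does not mention it. Report the baseline-CDI-only model as a sensitivity analysis.

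The cost is one sentence and a few degrees of freedom out of about 128 participants. No extra participants are needed.
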